### Frequency and plans for auditing trial conduct {23}

Auditing will be conducted only in case the funder or Ethical Committee requires.

### Plans for communicating important protocol amendments to relevant parties (e.g., trial participants and ethical committees) {25}

In this trial, important protocol modifications must be approved by the trial registry and the Ethical Committee.

### Dissemination plans {31a}

The study findings will be submitted for publication in peer-reviewed journals, irrespective of whether they support or challenge the initial study hypothesis.

## Discussion

The management of LARS is crucial considering its high prevalence and severe impairment of the quality of life [26]. The treatment timing is important, and early intervention for LARS is preferred as it is better for neural functions [27]. Therefore, as per our protocol, our intervention can start 1 month postoperatively for anal preserve rectal cancer or temporary ileal stoma retraction.

Opting for a combined approach of biofeedback and PEPNS for treating LARS is grounded in their potential synergistic action in LARS management as well as their high operational feasibility. Biofeedback, utilizing superficial electrodes and anal internal sensing probes, accurately detects pelvic muscle movements, providing effective guidance to patients during pelvic floor exercises. It also promotes pelvic muscle rehabilitation through superficial electrical stimulation. On the other hand, PEPNS precisely locates the perineal nerve positions via percutaneous needling, directly stimulating these nerves to increase the resting sphincter pressure, thereby enhancing bowel control. Biofeedback is a routine outpatient procedure conducted in many tertiary hospitals, whereas PEPNS implementation only requires an acupuncture apparatus and basic training for physicians in needling techniques, which can be easily sought in Chinese medicine hospitals. Hence, the execution of this study is comparatively straightforward.

The symptoms of LARS tend to be more severe in the initial months after surgery, especially in the first 4 months, followed by a gradual improvement and stabilization between 6 months to 1 year [4, 5]. Therefore, our assessments not only include a short-term evaluation 1 month after treatment but also a long-term evaluation after 6 months. This is aimed at minimizing potential biases due to natural symptom variations over time. Additionally, based on the results from the 6-month long-term evaluation, we will determine the necessity for further assessment after 1 year.

The selected outcome measures are based on their validity and reliability. The LARS score has been tested in the Chinese population and measured bowel dysfunction in patients after CRC surgery [23, 28]. This scoring system measures various aspects of postoperative bowel function, such as fecal incontinence, urgency of bowel movements, and bowel frequency, aiding physicians in evaluating the recovery and quality of life of patients postoperatively. A higher score indicates a more severe impact on the patient’s postoperative bowel function. ARM, the anorectal pressure measurement device, evaluates the strength, coordination, and reflex mechanisms of the anal sphincter muscles, pivotal for maintaining continence. [29]

The EORTC QLQ-CR29 is an evaluative tool used to gauge the multifaceted dimensions concerning treatment aspects and their influence on the daily lives of CRC patients. This comprehensive questionnaire covers distinct areas, encompassing symptomatic experiences, functional constraints, and emotional well-being directly associated with the ailment and its therapeutic interventions. Through its systematic inquiry method, the EORTC QLQ-CR29 assists in the meticulous assessment and resolution of the diverse array of challenges encountered by individuals undergoing CRC treatment. Its use helps in significantly fostering a more comprehensive and integrated approach toward patient care and therapeutic management strategies. [30]

Pelvic floor EMG is a diagnostic method assessing pelvic muscle activity via electrical signals. It evaluates the muscle strength, coordination, and relaxation patterns in pelvic floor disorders, such as incontinence. EMG aids in facilitating tailored treatments by providing precise muscle function insights, contributing to improved patient care.[31] 

Nevertheless, it is crucial to acknowledge certain limitations of this study, including potential variability in participant adherence and the absence of long-term follow-up data. Additionally, the inability to blind participants and therapists to the chosen treatment methods might introduce bias. However, efforts will be made to ensure independent data collection and processing, aiming to mitigate potential biases as much as possible.

In conclusion, this study protocol introduces a promising avenue for treating LARS, thus addressing a critical gap in the therapeutic options. The combination of biofeedback and PEPNS offers a potential breakthrough in non-surgical interventions. The findings of this RCT could provide clinicians with a more effective and patient-friendly approach when managing LARS.

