### Outcome {12}

Before commencing the treatment regimen, comprehensive patient information will be compiled, including demographic data, tumor metrics, surgical specifics, and any prior radiotherapy or chemotherapy received. Patients will undergo evaluations using the LARS and European Organization for Research and Treatment of Cancer Quality of Life Questionnaire-Colorectal 29 (EORTC QLQ-CR29) scoring systems along with anorectal manometry (ARM) and pelvic floor EMG assessments. These evaluations will be conducted at the following three key times: baseline, post-intervention (at 1 month), and during follow-up (at 6 months).

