## Assignment of interventions: allocation

### Sequence generation {16a}

Using SAS software (9.3), the Clinical Evaluation and Analysis Centre at SRRH will randomly allocate 242 participants in a 1:1 ratio to the intervention group (undergoing B-PEPNS) or the control group (undergoing biofeedback alone). Professionals overseeing allocation will not be directly involved in the study.

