#### Data processing and preliminary steps

Normality test: Data will be assessed for normality using the Shapiro-Wilk test.Handling baseline imbalances: If baseline characteristics and outcome measures show imbalances, analysis of covariance (ANCOVA) will be applied to adjust for these differences.Data presentation: Normally distributed continuous variables will be presented as means ± standard deviations (SD). Non-normally distributed or ordinal variables will be presented as medians with interquartile ranges (IQR). Categorical variables will be presented as counts and proportions.Missing data: The last observation carried forward (LOCF) method will be used to handle missing data points. Other rules are referenced in Item 20c.

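### Time since surgery drives natural recovery by the plan's own account; the 6-month visit cannot remove it, and adjustment should be pre-specified rather than triggered by imbalance

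*Protocol article*

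**What the plan says.** The inclusion criteria (Eligibility criteria {10}) require defecation dysfunction for at least 1 month after surgery and give no upper limit. The Discussion confirms the early start: "our intervention can start 1 month postoperatively for anal preserve rectal cancer or temporary ileal stoma retraction". The same section describes the natural course, with symptoms tending to be more severe in the initial months, "especially in the first 4 months, followed by a gradual improvement and stabilization between 6 months to 1 year". It then explains why a long-term evaluation is added to the short-term one: "This is aimed at minimizing potential biases due to natural symptom variations over time". Outcome {12} sets the assessments at "baseline, post-intervention (at 1 month), and during follow-up (at 6 months)".

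Sequence generation {16a} says the evaluation centre "will randomly allocate 242 participants in a 1:1 ratio to the intervention group (undergoing B-PEPNS) or the control group" and names no stratification factor. Primary outcome analysis fixes an independent-samples t-test, or Mann-Whitney test, between arms, and paired t-tests or Wilcoxon signed-rank tests before versus after treatment. The only adjustment rule is under Data processing and preliminary steps: "If baseline characteristics and outcome measures show imbalances, analysis of covariance (ANCOVA) will be applied to adjust for these differences". No covariate is named. The one subgroup factor, in {20b}, is radiotherapy. Baseline data include "demographic data, tumor metrics, surgical specifics, and any prior radiotherapy or chemotherapy received".

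**The concern.** The document itself identifies time since surgery (or since stoma reversal) as something that determines how far symptoms improve without treatment. It admits patients across the whole of that course, then relies on visit timing to deal with it. Visit timing does not help: the primary outcome is a change from baseline, and a longer interval adds natural recovery to that change.

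Two things are at stake. First, a known prognostic factor stays in the error term of the main comparison, in a trial sized for exactly 80% power. Whether it is adjusted for depends on what the baseline table happens to show. Second, a reader who accepts the Discussion sentence may take a significant before-after change within an arm at 6 months as a treatment effect, when it may be recovery.

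**Working it through.** **1. The plan's own figure.** Inputs from Sample size {14}: 65.6% v 46.7%, power 0.80, alpha 0.05 (two-sided, from Secondary outcome analysis), 1:1.

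n per arm = [0.656×0.344 + 0.467×0.533] × (1.960 + 0.842)² / 0.189² = 0.4746 × 7.849 / 0.03572 = 104.3, so 105 per arm and 210 in total. This matches the stated 210. (The pooled-variance formula gives 108 per arm, 216.) The starting power is therefore 80% at 105 evaluable patients per arm.

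**2. What the 6-month visit does.** A patient entering at month 1 has that visit at about month 7 to 8 after surgery, depending on whether it is counted from baseline or from the end of the 4 treatment weeks. That lies inside the document's own 6-to-12-month stabilisation window, so the change from baseline holds most of the natural recovery. A patient who enters after stabilisation contributes little or none. The later visit enlarges the recovery component for early entrants. In the difference between randomised arms, that component has the same expectation on both sides and cancels.

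**3. Chance imbalance.** The documents give no distribution of time since surgery, so assume a share q of early entrants. With unstratified allocation, the SD of the between-arm difference in that share is √[2q(1−q)/105]:
- q = 0.5: 6.9 points; 95% range ±13.5; chance of more than 10 points, 15%.
- q = 0.3 or 0.7: 6.3 points; 95% range ±12.4; chance of more than 10 points, 11%.

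Assume natural response differs by 10, 20 or 30 points between early and late entrants. At q = 0.5 the arm difference then moves by at most 1.4, 2.7 or 4.1 points (95% range), against a planned 18.9.

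This is not additional to the stated uncertainty. The standard error of the difference is √(0.4746/105) = 6.7 points. At a 30-point gap, imbalance contributes 0.30 × 6.9 = 2.1 points of it, and removing that leaves √(6.72² − 2.07²) = 6.4 points.

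**4. Precision gained by adjustment.** If the factor explains a fraction R² of outcome variance, power is Φ[2.802/√(1−R²) − 1.960]:
- R² = 0.05: 82%
- R² = 0.10: 84%
- R² = 0.15: 2.802/0.922 − 1.960 = 1.08, so 86%

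**5. Simulation with no treatment effect.** 4,000 runs, 105 per arm. Assumptions: entry uniform from 1 to 18 months; natural improvement of 30 points at month 1, decaying with a 4-month constant; residual SD 25. Time since surgery then explains about 8% of variance.
- Between arms, unadjusted: mean estimate 0.09, type I error 5.0%, SD 3.61.
- Between arms, adjusted for time: SD 3.46.
- Before-after test in the control arm: significant in 77% of runs, from recovery alone.

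The last figure checks by hand. Mean natural improvement is 30 × (4/17) × (1 − e^(−17/4)) = 7.0 points. The total SD is √(625/(1 − 0.084)) = 26.1, so the standard error is 26.1/√105 = 2.55 and the ratio about 2.7.

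**The case against.** A reader might infer that natural recovery biases the short- and long-term treatment effects. The documents do not support that. This is a concurrent 1:1 randomised comparison, time since surgery is balanced in expectation, and recovery occurs in both arms. The simulated type I error of 5.0% says the same. Shifts of a few points from chance imbalance are ordinary sampling error, already inside the standard error. This part of the objection stands in full.

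It is also fair that the analysis is not silent: the ANCOVA rule could take in time since surgery, and the surgical data collected may well include the date. Nor does the article say that allocation is simple; it names no stratification factor, and a condensed article may leave that out. Absence of stratification is therefore not held against the plan.

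What does not fall away is what the article fixes. It states unadjusted tests, makes adjustment depend on observed imbalance, and gives a wrong reason for the 6-month visit. An imbalance trigger forgoes the precision gain in the usual case where arms look similar. ANCOVA also does not carry over to the Mann-Whitney route or to a responder criterion of more than 25% improvement.

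Finally, the 6-month visit is informative in itself: if the combination merely speeds recovery, the arms among early entrants should converge by then. That is a reason to keep the visit, but it shows in the between-arm contrast, not because the visit removes natural change.

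**Conclusion.** The concern holds as one of efficiency and interpretation. The 6-month visit does not minimise natural-course bias; the randomised control does. The between-arm estimate is unbiased at both visits but less precise than it need be. Adjustment would raise power from 80% to roughly 82–86% if time since surgery explains 5–15% of outcome variance. That range is an assumption, since the documents give neither the spread of entry times nor the size of natural recovery. The paired within-arm tests are confounded with recovery. The 77% figure depends on the simulation's assumptions, but the confounding does not. Pre-specified adjustment is a modest gain at almost no cost.

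**What to change.** 1. In Data processing and preliminary steps and in Primary outcome analysis, replace the imbalance-triggered rule with one pre-specified between-arm model for the primary outcome at 1 and 6 months. Include arm, baseline LARS score, and time at randomisation since surgery (since stoma reversal where there was one), whether or not imbalance is seen. Fix the form of the time term in advance and allow for flattening, for instance log months. If the responder criterion is to be the primary measure, use the same covariates and report an adjusted risk difference.
2. Rest conclusions on the between-arm contrast. Keep the paired tests as description only and say that they are not estimates of treatment effect.
3. Correct the Discussion sentence so that it credits the concurrent control and the adjustment, not the later visit.

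The cost is small. The timing is already needed to check eligibility, the model applies to every enrolled patient, and the change can be made before analysis. It does need the registry and Ethics Committee approval that the protocol requires for important modifications.

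Stratifying the remaining allocation is optional and of little value: recruitment began in February 2023 and is due to end in January 2025, and the article appeared in July 2024. An early-versus-late interaction estimate may be reported as exploratory only, since the trial is sized for the main effect.

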## Trial status

This is protocol version 1, 1 January 2022. Trial recruitment commenced on February 5, 2023, and is scheduled to conclude by January 31, 2025.

## Data Availability

The datasets generated and/ or analyzed during the study will be available on reasonable request. Data can be obtained by contacting the main researcher. Email for requests: [contact].

## Abbreviations

LARS: Low anterior resection syndrome
PEPNS: Percutaneous electrical pudendal nerve stimulation
B-PEPNS: Biofeedback with percutaneous electrical pudendal nerve stimulation
ARM: Anorectal manometry
EMG: Surface electromyography
EORTC QLQ-CR29: European Organization for the Research and Treatment of Cancer Quality of Life Questionnaire-Colorectal 29
